## Abstract

Obesity is a major risk factor for obstructive sleep apnoea (OSA), the most common sleep-disordered breathing related to neurocognitive and metabolic syndromes, type II diabetes, and cardiovascular diseases. Although strongly recommended for this condition, there are no studies on the effectiveness of an interdisciplinary weight loss and lifestyle intervention including nutrition, exercise, sleep hygiene, and smoking and alcohol cessation. INTERAPNEA is a randomised controlled trial with a two-arm parallel design aimed at determining the effects of an interdisciplinary tailored weight loss and lifestyle intervention on OSA outcomes. The study will include 84 males aged 18–65 with a body mass index of ≥25 kg/m^2^ and severe to moderate OSA randomly assigned to usual care (i.e., continuous positive airway pressure), or interdisciplinary weight loss and lifestyle intervention combined with usual care. Outcomes will be measured at baseline, intervention end-point, and six-month post-intervention, including apnoea-hypopnoea index (primary outcome), other neurophysical and cardiorespiratory polysomnographic outcomes, sleep quality, daily functioning and mood, body weight and composition, physical fitness, blood biomarkers, health-related quality of life, and cost-effectiveness. INTERAPNEA may serve to establish a cost-effective treatment not only for the improvement of OSA and its vast and severe comorbidities, but also for a potential remission of this condition.

## 1. Introduction

Obstructive sleep apnoea (OSA), produced by repeated upper airway collapse during sleep, has increasingly become the focus of numerous current interdisciplinary research attributed not only to its high prevalence, but also to the wide range of adverse health consequences of this condition [1]. The repeated events of complete (apnoea) or partial (hypopnoea) pharyngeal obstruction that occur while sleeping lead to intermittent hypoxic episodes, hypercapnia, sleep fragmentation, and upsurges of sympathetic activity [2]. Driven by these short-term consequences, OSA is closely related to increased morbidity and mortality [3], including cardio-metabolic disorders [4], neurocognitive abnormalities [5], impaired daily functioning and mood [6], and greater risk of vehicle and occupational accidents [7,8]. 

It has recently been estimated that up to 38% of adults suffer from OSA, being more prevalent in males, the elderly, and in those who are obese [9]. Therefore, OSA risk factors include obesity, sex, age, and adverse lifestyle habits such as sedentariness, poor nutrition, smoking, and alcohol intake [10]. According to epidemiological studies, nearly 60% of moderate to severe OSA is attributable to obesity [11], which contributes to alterations of the airway anatomy and collapsibility, respiratory modulation, resting lung volume, and neurohormonal mediators on ventilation [12]. Given the exponential increase of obesity prevalence in the overall population, which has nearly tripled since 1975—in 2016 39% of adults aged 18 years and over were obese—OSA prevalence is not only worryingly high but also likely to rise in the upcoming years [13].

The current treatment of choice is continuous positive airway pressure (CPAP) [14], a mechanical device used to maintain upper airway patency, thereby improving the main symptoms and consequences of OSA through the reduction of the number of apnoea-hypopnoea episodes per hour of sleep (i.e., apnoea-hypopnoea index, AHI) [15,16,17]. However, CPAP is a chronic day-to-day treatment—it does not cure OSA in the long-term—and its use may be rejected or abandoned due to discomfort and/or other inconveniences [18]. Most importantly, CPAP does not address the major high-risk factors of OSA, i.e., obesity and adverse lifestyles.

Hence, alternative or combined behavioural interventions including weight loss through dietary approaches and exercise, sleep hygiene, and avoidance of alcohol and tobacco consumption are required and strongly recommended in the most recent practical guidelines from the American Academy of Sleep Medicine (AASM) [14,19]. According to our recently published systematic review and meta-analysis on the effectiveness of these interventions [1], the combination of diet and exercise may be an effective treatment in improving OSA outcomes in middle-aged males with moderate to severe OSA.

Yet, the number of reported randomised controlled trials addressing both diet and exercise components as a combination was significantly low and only included effects on specific OSA outcomes such as AHI, oxygen desaturation index, and excessive daytime sleepiness [1]. Furthermore, no original studies actively focusing on the cessation of tobacco and alcohol consumption were found [1], factors which have been shown to be common in patients with OSA and associated with the worsening of this condition [20,21]. Thus, the actual effectiveness of potential interdisciplinary interventions for the improvement of the main symptoms and consequences of OSA still remains unclear. Considering the vast and severe OSA consequences and comorbidities, with obesity being a major risk factor for this condition, there is a need for well-designed studies comprising all of these aspects and evaluating the potential clinical and economic relevance of these interventions for OSA and related diseases. 

The INTERAPNEA randomised controlled trial (RCT) is aimed at implementing and testing the effectiveness of an eight-week interdisciplinary weight loss and lifestyle intervention on overweight-obese adults with CPAP-treated moderate to severe OSA. This intervention will include nutritional behaviour change, supervised-exercise, sleep hygiene, and active alcohol and tobacco cessation components, comparing the impacts on primary and secondary OSA outcomes to the standard care, i.e., CPAP therapy. Furthermore, INTERAPNEA not only pursues to analyse the effect of this intervention on OSA outcomes but also on the overall physical and psychological health of patients with moderate to severe OSA.

## 2. Methods

### 2.1. Study Design

The INTERAPNEA study (ClinicalTrials.gov ID: NCT03851653) is an RCT with a two-arm parallel design where participants will be randomly allocated to a usual care/control group (i.e., CPAP therapy) or an 8 week interdisciplinary weight loss and lifestyle intervention combined with CPAP. The study conforms to the last revised Ethical Principles for Medical Research Involving Human Subjects comprised in the Declaration of Helsinki, and approval of the study protocol was obtained from the Clinical Research Ethics Committee of the “Junta de Andalucía” (0770-N-19). All participants will receive accurate information on the study assessments and intervention, and written informed consent from each participant will be obtained prior to any data collection.

### 2.2. Study Organisation and Coordination Centre 

Adults diagnosed with moderate to severe OSA potentially meeting the inclusion criteria will be recruited from the “Virgen de las Nieves” University Hospital (Granada, Spain). Data collection at baseline and follow-ups, as well as implementation of the intervention, will be performed in two different settings of the University of Granada (Granada, Spain): Sleep and Health Promotion Laboratory of the Mind, Brain, and Behaviour Research Centre (CIMCYC), and Sport and Health University Research Institute (iMUDS). The Sleep and Health Promotion Laboratory is the coordinating centre for the study, responsible for the study design and organisation, patient recruitment process, data collection and management, randomisation and participant allocation, trial monitoring, and reporting of the study process and results.

### 2.3. Participants and Selection Criteria

Eligible participants will be adults previously diagnosed with moderate to severe OSA (AHI equal or greater than 15 [22]) from the province of Granada (Spain). They must be between 18 and 65 years old, and have a body mass index (BMI) equal to or greater than 25 kg/m^2^. A full list of the study’s inclusion and exclusion criteria are shown in Table 1. Due to the well-evidenced higher incidence and prevalence of OSA in males [9], and the differences in OSA phenotypes between men and women [23], we decided to include only male participants in the study. Furthermore, the effectiveness of non-pharmacological and non-surgical weight loss interventions have been shown to be less effective in women [1,24], such that different approaches are needed in this population with OSA.

Potential participants will be medically examined and must complete a health history revision prior to their inclusion in the study in order to ensure no hindrance/harm related to the assessment and intervention protocols. Should any incident or medical problem arise during the intervention, participants will be physically and psychologically examined and, if necessary, excluded from the study. A clinical trial liability insurance will be contracted for the INTERAPNEA study, providing legal and financial protection to the sponsor-investigators, and compensation to participants in the case of an injury or any damage incurred in and as a result of the study.

### 2.4. Recruitment and Randomisation 

#### 2.4.1. Sample Size

The sample size calculation and power of the study are based on the data of previously reported studies contrasted, combined, and synthesised in our recent systematic review and meta-analysis [1]. We considered following the formula $n=\;\frac{2{\left(Z_{\alpha }\;+\;Z_{1-\beta }\right)}^{2}\sigma^{2}}{\Delta^{2}}$, where *n* is the required sample size, *Z_α_* and *Z*_(1 − *β*)_ are the constants set by convention according to the accepted *α* error and power of the study, respectively, *σ* is the estimated standard deviation, and Δ is the expected effect size. Therefore, we expect to detect an effect size of −8.36 on AHI (pooled raw mean difference of previous trials) [1], considering a type 1 error/α error of 5% (*Z_α_* = 1.64), and a statistical power of 90% (*Z*_(1 − *β)*_ = 1.28). Regarding the estimated AHI variability, we established an *σ* of 11.98, considering the AHI pooled standard deviation of all independent samples included in our previous research [1]. As a result, the expected sample size is ≈35 participants per arm of our controlled clinical trial. However, assuming a maximum of a 17.25% drop-out rate (based on the average drop-out rate of previous studies [1]), we decided to recruit a total sample size of ≈42 participants for each study group. Thus, a total of ≈84 patients with moderate to severe OSA will be enrolled in the INTERAPNEA study. For practical and feasibility reasons, and based on our previous experience [25,26], the study will be conducted in sets of a maximum of 30 persons.

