### 2.9. Analytical Approach and Statistical Power/Data Management

We will perform descriptive and exploratory preliminary analyses of all the study variables to reveal violations of statistical assumptions, distributions, imbalances between the study groups, associations between study variables, covariates/confounders, amount of missing data, and drop-out patterns. Covariates or confounders will be secondarily included in the main statistical analysis, evaluating therefore, their impact on the results. To ensure that conclusions are robust, attrition bias will be overcome through intention-to-treat-analysis (ITT), including all participants as originally allocated after randomisation using multiple imputation methods for predicting end-points missing values. Per-protocol comparison of groups, including only those participants who fully completed the originally allocated treatment, will also be computed and compared with ITT analysis results.

The intervention effects on primary and secondary study outcomes will be assessed through multi-level mixed analyses using the package *nlme* [96] from the R statistical program. This method will allow us to analyse differences including time and group allocation as within and between subject factors, respectively, adjusting for potential covariates and levels such as group or set of participants. Therefore, group/condition will be considered as a fixed variable (intervention group compared to control group), and sets/waves of participants as a random factor. With these specifications, we will be able to control the intra-class correlation (per set of participants nested within conditions) between scores at baseline and post-test or follow-up. We will adjust the model including the baseline values of outcomes that are to be analysed in the specific analysis as covariates, as well as other potential covariates such as age, OSA severity, BMI, motivation to change, and attrition propensity. The latter will be calculated using a model predicting the actual attrition with baseline values [97]. Baseline measurements included in these attrition propensity prediction models will include set of participants, participant’s allocation, age, OSA severity, BMI, and motivation to change. The primary and secondary study outcomes that are to be analysed will be those previously mentioned in the outcomes section.

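### The stated 90% power rests on the one-sided 5% value (Z = 1.64) although no one-sided test is declared; for a two-sided 5% test the same formula and inputs give about 82–83%

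*Protocol article*

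**What the plan says.** Section 2.4.1 prints the usual formula for comparing two means and all its inputs. The target is set by "we expect to detect an effect size of −8.36 on AHI (pooled raw mean difference of previous trials"), the SD is 11.98, and the constants are fixed by "considering a type 1 error/α error of 5% (*Z_α_* = 1.64), and a statistical power of 90" per cent, the latter with Z = 1.28. The conclusion is that "the expected sample size is ≈35 participants per arm of our controlled clinical trial". After an allowance for 17.25% drop-out, "we decided to recruit a total sample size of ≈42 participants for each study group", or 84 in total.

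Section 2.9 assesses the primary and secondary outcomes through "multi-level mixed analyses using the package" nlme in R. It explains: "This method will allow us to analyse differences including time and group allocation as within and between subject factors". The model also adjusts for the baseline value of the outcome and other covariates. Neither section says whether the test is one-sided or two-sided, and nor does the rest of the article.

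**The concern.** A 5% type I error with no further qualification is normally read as two-sided. The printed constant contradicts that reading: 1.64 leaves 5% in one tail, so a two-sided test with that cut-off has a type I error of 2 × 5% = 10%. The error rate and the constant agree only if a one-sided test is meant, and the article never says so.

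The affected figure is the power statement for the primary outcome, which readers will use to interpret a result that is not significant. A reader who assumes a two-sided test would think that a true difference of 8.36 events/h is missed 1 time in 10, when the sample-size formula puts it nearer 1 in 6. Silence on sidedness also leaves the significance threshold ambiguous by a factor of two, and open to being settled after the data are seen.

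**Working it through.** **Inputs, all from section 2.4.1:** difference Δ = 8.36 events/h (absolute value), SD σ = 11.98, Z for power = 1.28, Z for α = 1.64, completers per arm n = 35, drop-out 17.25%.

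**Step 1. Reproduce the plan's figure.** The formula is n = 2(Zα + Z1−β)²σ²/Δ².
- With Zα = 1.64: 2 × (1.64 + 1.28)² × 11.98² / 8.36² = 35.02 per arm. This matches the stated figure.
- With Zα = 1.96: 2 × (1.96 + 1.28)² × 11.98² / 8.36² = 43.1 per arm. This cannot be read as about 35.

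So the stated sample size is a one-sided 5% calculation.

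**Step 2. Power at 35 completers per arm.** The standard error of the difference is 11.98 × √(2/35) = 2.864, and 8.36 / 2.864 = 2.919.
- One-sided 5%: Φ(2.919 − 1.64) = Φ(1.279), about 90%. The noncentral t gives 89.3%. The stated power is right for this test.
- Two-sided 5%: Φ(2.919 − 1.96) = Φ(0.959) = 83.1%. The noncentral t with 68 degrees of freedom gives 82.1%.

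On the unadjusted formula, the two-sided type II error is therefore about 17–18%, against 10% stated.

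**Step 3. What two-sided 90% power would need.** About 43–44 completers per arm: 43.1 by the printed formula, 44 with unrounded normal quantiles and rounding up. Dividing by 1 − 0.1725 = 0.8275 and rounding up gives 53–54 recruited per arm, against 42 planned.

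**Step 4. What 35 per arm can detect with two-sided 90% power.** (1.96 + 1.28) × 2.864 = 9.28 events/h by the normal approximation, or 9.42 by the t test, so about 9.3–9.4 against the planned 8.36.

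**Step 5. What baseline adjustment could recover.** Under a simple covariance adjustment the residual SD is σ√(1 − ρ²), where ρ is the baseline-to-follow-up correlation. Two-sided 90% power for 8.36 at 35 per arm needs √(1 − ρ²) to be no more than 8.36/9.28 (normal) or 8.36/9.42 (t). That gives ρ of at least about 0.43 or 0.46 respectively. The article reports no correlation, so whether this is met is an assumption.

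**The case against.** **A one-sided test may have been intended.** The primary outcome is framed as a reduction in AHI, the expected effect carries a minus sign, and the discussion speaks of demonstrating benefit. If so, the inputs are consistent and 90% is correct. This part stands: the article never says that a two-sided test will be run. That is an inference from its silence and from a model described without a direction. A reader might conclude that the trial's power is simply misstated, or that its inputs fail to deliver 90%. The documents do not support this, because 1.64 is one of the inputs and with it the figure reproduces. But an expected direction does not declare a one-sided test, so the text still needs correcting.

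**The 82–83% is not the power of the planned analysis.** This also stands. It belongs to the unadjusted comparison of two means that section 2.4.1 uses, whereas section 2.9 adjusts for baseline in a mixed model. A reader might infer that the true power of the trial is 82%, but the article gives neither the correlation nor the intra-class correlation needed to say so. Equally, a gain from adjustment that was not used in the calculation cannot support the printed 90%.

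**Multiple imputation retains everyone randomised.** Imputation does not restore the outcome information that is lost. Even with all 42 per arm observed, two-sided power would be 89.2% (normal) or 88.5% (t).

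**Such detail may sit in an analysis plan not shown.** That could excuse silence on sidedness alone. It does not excuse printing an unqualified 5% beside a one-sided constant and a power figure that depends on it.

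Two further criticisms are tempting and should not be made. The drop-out step (35/0.8275 = 42.3, taken as about 42) is rounding. A figure for power lost to clustering by set would need intra-class correlations and set sizes that the article does not give.

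**Conclusion.** The point holds in a limited form. The 90% power at 35 completers per arm is valid only for a one-sided 5% test, which the article does not declare. Under a conventional two-sided 5% test, the same formula, difference and SD give about 82–83%, a shortfall of 7 to 8 percentage points. The conclusion rests on the article's own inputs, on 35 evaluable patients per arm, and on an unadjusted comparison. Whether the planned adjusted model reaches 90% in a two-sided test cannot be settled from the document.

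**What to change.** Keep 84 patients and state the sidedness of the primary test in both section 2.4.1 and section 2.9.

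- **If two-sided:** replace the power statement with wording such as: with a two-sided α of 5%, 35 completers per arm give about 82–83% power to detect 8.36 events/h (SD 11.98) without baseline adjustment. Alternatively, give the difference detectable with 90% power, about 9.3–9.4 events/h. The text may add that baseline adjustment could recover 90% if the baseline-to-follow-up correlation is about 0.43–0.46 or more, labelled as an assumption.
- **If one-sided:** keep 1.64 and 90%, and declare the one-sided 5% test and its direction before analysis.

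The cost is a few words in two sections. No patients are added and the analysis model is unchanged. On the two-sided route, the price is a less favourable power statement.

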#### 2.4.2. Source of Participants

The recruitment of participants will be performed using different strategies including enrolment from the collaborating hospital sleep unit, and use of mass media (e.g., press, magazines, radio and television news, and websites). A brief in-person or phone screening will be conducted on potentially interested participants to provide general information about the study and determine suitability of inclusion. Patients willing to participate and appearing to meet the inclusion criteria will be required to attend an in-person briefing on the rationale and study aims, inclusion and exclusion criteria, assessments to be performed, and components and characteristics of the intervention. After clarification by the research staff of any participant’s doubts or questions, signatures of informed consent will be obtained from participants that meet the eligibility criteria, and appointments for the baseline assessment will be given. Participant flow from recruitment to randomisation stages are shown in Figure 1.

#### 2.4.3. Enrolment

Upon obtaining signed informed consents, participant demographics and medical history will be collected, and a medical/physical examination will be performed to ensure feasibility of participant inclusion in the study. Subsequently, a sleep study through a complete full-night polysomnography and other sleep measurements (daytime sleepiness, sleep quality, circadian preference, functional outcomes of OSA) will be conducted on and taken from each participant. Furthermore, lifestyle habits such as diet, exercise, and tobacco and alcohol consumption will also be measured, as well as subjective health-related quality of life, and depressive and anxiety symptoms related to OSA. After completion of participant’s medical and sleep studies, objective measurements of cardiorespiratory fitness and body composition will be taken from each participant. All test trials will be scheduled over three different days during a one to two-week period.

#### 2.4.4. Randomisation and Blinding

After completing baseline measurements, eligible participants will be randomly assigned to either a control group or an interdisciplinary intervention group using computer generated simple (unrestricted) randomisation [27]. Each participant will be specifically informed of which arm they have been assigned to and requested not to reveal their allocation to the research staff involved in further assessments. Bias related to unblinded participants, treatment counsellors and/or outcome assessors affecting data validity will be addressed by achieving different levels of blinding across the study personnel and participants, where feasible. Therefore, study personnel responsible for data collection and analysis will be blinded to allocation assignments at the follow-ups, and blinding of participants to details of study manuals and hypothesis will be attained. When blinding is not possible, rigorous procedures of standardisation of data collection and intervention, through study manuals and continuous assessment of fidelity, will be followed to avoid potential bias and ensure internal and external validity of the study [28].

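### Unrestricted randomisation leaves arm sizes to chance, overall and within each set; allocating 1:1 within set would be a cheap improvement

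*Protocol article*

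**What the plan says.** All references are to the protocol article.

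- **Allocation (2.4.4).** Men are "randomly assigned to either a control group or an interdisciplinary intervention group using computer generated simple (unrestricted) randomisation". This names the method and rules out blocking and stratification, so it is not a detail lost in condensing a longer protocol. Timing is also given: "After completing baseline measurements, eligible participants will be randomly assigned". Each man is told his arm.
- **Size and sets (2.4.1).** The calculation gives about 35 per arm. After allowing for 17.25% drop-out, the article states that "we decided to recruit a total sample size of ≈42 participants for each study group", about 84 in all. For feasibility, "the study will be conducted in sets of a maximum of 30 persons".
- **Delivery (2.6, 2.8).** The modules are given as group sessions, each supervised by a pair of providers.
- **Analysis (2.9).** The mixed model takes "sets/waves of participants as a random factor" and adjusts for the baseline value of the outcome. Age, OSA severity and BMI are listed as further potential covariates. Sets are described as nested within condition.

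**The concern.** The plan treats set as a source of correlation in the analysis and as the unit in which the trial is run, but the allocation ignores it. Under unrestricted allocation, 42 per arm is only an expected value, and the split within a set can be well away from even.

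Three things are at stake, none of them large:

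- some precision, mainly if set is adjusted for;
- a chance association between arm and set, which the model must absorb with a variance estimated from perhaps three sets;
- the size of each intervention class, which allocation alone determines within a set.

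**Working it through.** **Inputs.** From 2.4.1: difference 8.36 events/h, SD 11.98, Z values 1.64 and 1.28, drop-out 17.25%, 84 men in total, sets of at most 30. From 2.4.4: independent allocation, taken as probability 0.5 because equal arms are planned. Assumption: three sets, because 84/30 = 2.8 and the number of sets is not stated. Sets of 28/28/28 are used, with 30/30/24 as a check.

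**1. The plan's own figure.** n = 2(1.64 + 1.28)² × 11.98² / 8.36² = 35.02 per arm. Then 35/0.8275 = 42.3, so 42 per arm and 84 in total. The stated figures reproduce. The constant 1.64 is the one-sided value and the article does not name sidedness, so power is given both ways below. Sidedness is a separate matter from allocation.

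**2. Overall arm sizes, Binomial(84, 0.5).**

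| Quantity | Result |
|---|---|
| P(exactly 42/42) | 8.7% |
| P(both arms between 40 and 44) | 41% |
| Expected absolute difference | 7.3 men |
| P(smaller arm ≤ 36) | 23% |
| P(smaller arm ≤ 33) | 6.3% |
| 95% range | 33/51 to 51/33 |

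**3. Within sets.** For Binomial(28, 0.5), an even 14/14 split has probability 15%, and the 95% range is 9/19 to 19/9. P(9/19 or worse) = 8.7%, so over three sets 1 − (1 − 0.087)³ = 24%. P(at least one set at 10/18 or worse) = 46%. Sets of 30/30/24 give the same 24% and 46%.

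**4. Arm-set association.** In 200,000 simulated allocations, the R² of arm on set has a median of about 0.015 to 0.017 and a 95th percentile of about 0.07 (correlation about 0.27). The chance that any set falls wholly in one arm is 3 × 2/2²⁸ ≈ 2 × 10⁻⁸ for sets of 28, and about 10⁻⁷ for 30/30/24.

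**5. Power.** Use Φ(Δ/SE − z) with SE = σ√(1/n₁ + 1/n₂) and 82.75% of each arm completing. At 42/42 there are 34.755 completers per arm, so SE = 11.98 × √(2/34.755) = 2.874 and Δ/SE = 2.909. Power is Φ(2.909 − 1.645) = 89.7% one-sided and Φ(2.909 − 1.960) = 82.9% two-sided.

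| Allocation | One-sided | Two-sided |
|---|---|---|
| 42/42 | 89.7% | 82.9% |
| 38/46 | 89.5% | 82.5% |
| 36/48 | 89.2% | 82.1% |
| 33/51 | 88.4% | 81.1% |
| Average, simple randomisation | 89.4% | 82.4% |
| Average, simple, adjusted for three sets | 88.7% | 81.5% |

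The average loss is therefore 89.7 − 89.4 = 0.3 points one-sided (82.9 − 82.4 = 0.5 two-sided). With set as a fixed adjustment it is 1.0 point (1.4 two-sided). In the least favourable 2.5% of allocations, set-adjusted power is about 86.4% or lower one-sided (78.3% two-sided).

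**6. Sensitivity to the number of sets.** With m sets, the expected set-adjusted information under simple allocation is Σ(nᵢ − 1)/4 = (84 − m)/4, against 84/4 = 21 when every set is balanced. The ratio is (84 − m)/84: 96.4% for three sets, 95.2% for four and 92.9% for six. More and smaller sets raise the cost, but slowly.

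**The case against.** The strongest reply is that nothing here is wrong. Simple randomisation is valid and offers the least predictability, which matters when men know their arm. The article says approximately 42, so an expected 42 does not contradict it, and an exact split is never required. Set and baseline AHI are already in the model, and the power at stake is slight. The article gives no minimum or maximum class size. Attendance at the tobacco and alcohol modules also depends on smoking and drinking status, which balanced arms would not settle. All of this stands, and it limits the point to an improvement.

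Three stronger readings are tempting and are not supported:

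- **Arm is confounded with set.** A reader might infer this from an uneven split. Allocation is independent of set, the association is weak (95th percentile R² about 0.07), and each set will almost certainly contain both arms.
- **The sample size fails.** A reader might infer this from the 8.7% chance of an exact 42/42. The plan states an approximate target, and even 33/51 costs only 1.3 points one-sided (1.8 two-sided).
- **Chance imbalance drives the flexible covariate choice in 2.9.** That wording would read the same under blocked allocation and is a separate matter.

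The reply does not fully cover the analysis. A between-set variance from about three sets is poorly estimated. Sets described as nested within condition, read literally, would not cleanly remove a set effect shared by both arms. Balance within set makes the comparison much less dependent on how that term is specified. The predictability argument also falls away if a whole set is allocated at once.

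**Conclusion.** The point holds as a cheap design improvement. Section 2.4.4 fixes a method that takes no account of the sets in which the trial is run and analysed. It leaves an expected difference of 7.3 men between arms, a 23% chance that the smaller arm has 36 or fewer and, with three sets of 28, a 24% chance of a 9/19 split or worse in at least one set. The price is about 0.3 points of power on average, or 1.0 to 1.4 points if set is adjusted for, together with less even class sizes. Validity is not threatened, and the stated sample size is not in error on this account.

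The overall figures rest on 84 men allocated independently with probability 0.5. The per-set figures also rest on three sets, which is inferred from the maximum of 30. The power figures use the article's difference, SD and drop-out rate, equal drop-out in both arms and a normal approximation. They take no credit for precision gained from baseline adjustment.

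**What to change.** In 2.4.4, replace unrestricted allocation with 1:1 randomisation within each set. Preferably allocate a set as one batch after all its men have completed baseline; otherwise use permuted blocks of random size within set. Three sets of 28 would then give 14/14 each and 42/42 overall. Keep set and baseline AHI in the model. Stratifying by moderate versus severe OSA is optional: baseline AHI is already adjusted for, and the article does not give the severity mix from which a further gain could be calculated.

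The cost is a different list generator. Batch allocation also means that the first men to finish baseline wait for the last in their set. The downside of sequential blocking is slight predictability, which random block sizes limit and batch allocation avoids. The change must be made before a set is allocated.
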